### **8.3 Assessment during the treatment period**

#### **Follow-up assessment—Clinical**

Standardized Clinical Follow-up Protocol - At the three month follow-up, patients will undergo a standard history and physical exam including digital rectal examination performed by the treating physician. Serum and red blood cells will be drawn for PSA, testosterone, estrogen, lycopene, omega-3 fatty acid, omega-6 fatty acid, IGFBP-3, and IGF-1 levels. Patients will have a second appointment for research purposes only, with a study urologist ([name] or another urologist from the UCSF Urologic Oncology Department) who will obtain four directed prostate core needle samples under ultrasound guidance in order to re-biopsy the areas of tumor and normal prostate identified at the baseline visit to fulfill the study primary outcome measure of detecting gene expression modulation by nutrients. Tissue biopsies for research purposes will also be sent for standard pathologic examination. As obtaining biopsies three months after electing Watchful Waiting is not standard practice, the study will bear costs for the biopsy procedure. In addition to any prostate biopsy obtained above, serum and urine will be obtained and frozen for future analysis. Patients will fill out a second food diary during the second month of treatment intervention and a third food diary prior to their biopsy. These food diaries will be used to collect information about changes in dietary behavior associated with recent diagnosis with prostate cancer, dietary counseling, or participation in this trial. Patients will complete another Health and Prostate Cancer Survey after three months. Patients will also be asked to self-report their compliance with the study treatment, and to return their medicine so that pill counts can be performed. Based on the results of the three-month follow-up visit, serum and pathology tests, the treating physician will assess the patient for disease progression.

### **Follow-up assessment—Molecular**

We will assess compliance and effectiveness of the nutritional supplements by measuring serum levels of lycopene, omega-3 and omega-6 fatty acids at baseline and post-intervention.

All of the procedures for follow-up tissue processing are identical to those for baseline assessment. In addition, we will examine in detail the nutritional effect on gene expression in molecular pathways known to play a critical role in the formation of tumors such as the cell cycle, apoptotic and DNA repair pathways. For this analysis we have implemented automated pathway mapping software from the Conklin laboratory at UCSF. The GenMapp software package ([www.genmapp.org](http://www.genmapp.org)) maps gene expression results from arrays onto pathways that can be customized or written entirely by the user, providing graphic output with gene expression ratios color coded on pathway diagrams. Using GenMapp, we have shown specific defects in the apoptotic pathway, the androgen receptor pathway, and the TGF-beta pathway in hormone sensitive and refractory prostate cancer patients.

### **8.4 Early termination or final visit**

Patients may terminate the study at any time for any reason. Patients finishing the 3 month intervention and 21 month monitoring period without progression will be offered standard care for their prostate cancer.

### **8.5 Additional safety follow-up**

None.

### **8.6 Study table: timing of physical exam, labs, transrectal ultrasound and biopsy**

The dietary intervention and molecular analysis will be complete within approximately three months for each patient. We anticipate that it will take up to three years to accrue the target number of patients and conduct the molecular analysis. Patients remaining on the watchful waiting protocol—regardless of assignment to control or intervention arms—will be followed indefinitely according to UCSF standard of care in the Urologic Oncology program.

# STUDY TABLE:

|                                                                       | +/-1-4 week(s) | +/-3 months@   | +/-6 months | +/-9 months | +/-12 months   | Continuing a |
|-----------------------------------------------------------------------|----------------|----------------|-------------|-------------|----------------|-------------------------|
| Office Visit with Vital Signs                                         | X              | X              | X           | X           | X              | X a          |
| TRUS-biopsy                                                           | X b | X g |             |             | X c | X a          |
| PSA                                                                   | X d | X              | X           | X           | X              | X a          |
| Digital Rectal Exam                                                   | X              | X              | X           | X           | X              | X a          |
| Food Questionnaire                                                    | X              |                |             |             | X              |                         |
| Health and Prostate QOL                                               | X              | X              |             |             |                |                         |
| Pill Counts                                                           |                | X              |             |             |                |                         |
| Microarray                                                            | X              | X              |             |             |                |                         |
| Serum Testosterone                                                    | X              | X              | X           |             | X              |                         |
| Serum Estradiol                                                       | X              | X              | X           |             | X              |                         |
| Serum lycopene                                                        | X              | X              | X           |             | X              |                         |
| Serum IGFBP-3                                                         | X              | X              | X           |             | X              |                         |
| Tissue Cox-2                                                          | X              | X              |             |             |                |                         |
| Tissue IGF-1                                                          | X              | X              |             |             |                |                         |
| Serum IGF-1                                                           | X              | X              | X           |             | X              |                         |
| Serum Omega3/6 ratio                                                  | X              | X              | X           |             | X              |                         |
| Placebo or nutritional supplement and MVI administration e | X              |                |             |             |                |                         |
| Dietary Counseling                                                    | X              |                |             |             |                |                         |
| Serum banking f                                            | X              | X              | X           |             | X              |                         |
| Urine f                                                    | X              | X              |             |             |                |                         |

|  |                |              |             |             |              |                         |
|--|----------------|--------------|-------------|-------------|--------------|-------------------------|
|  | +/-1-4 week(s) | +/-3 months@ | +/-6 months | +/-9 months | +/-12 months | Continuing a |
|--|----------------|--------------|-------------|-------------|--------------|-------------------------|

aafter the completion of the 3 month intervention period, patients will be referred back to their primary UCSF urologist for further care, which may include the indicated assessments.

bpatients who have donated prostate needle biopsy tissue within 3 months of study entry to the existing Prostate Cancer Tissue Bank will not undergo the initial TRUS biopsy, since their gene expression pattern will have already been comprehensively assessed, and RNA for the primary study aims banked.

cneed for the 12 month TRUS biopsy will be determined by the PSA progression criteria in section 9.4. Some patients, specifically those whose PSA doubling time remains > 12 months at the final study visit will not be asked to undergo the 12 month biopsy.

d three serum PSAs at least 2 weeks apart over the past year to permit calculation of a PSA doubling time [77] must be available. For those patients without serial PSA measurements, randomization will be delayed until collection of the third PSA. Patients with PSA doubling time < 3 months are ineligible to participate.

ePatients will remain on the assigned intervention – placebo, lycopene or fish oil, until the follow-up appointment for transrectal ultrasound and prostate biopsy occurs. Due to scheduling constraints, such as the occurrence of weekends or holidays, it is anticipated that some patients may have to stay on supplement between one to two weeks longer than the literal three month period. Any patient where repeat biopsy cannot be obtained by 14 weeks after beginning intervention will be censored.

fSerum and urine are banked at study entry but not used in the primary data acquisition. These resources are anticipated for possible future confirmatory studies if predictors of progression are identified. Patients will initial their consent for these samples at the end of the informed consent form.

gThe three month research biopsies will be performed at no cost to the participating study subjects.

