## **Phase I trials**

Recently a small clinical study of 15 men assigned supplement and 11 controls showed a decrease in PSA, decrease in tumor volume and decrease in IGF-1 levels after 3 month consumption prior to radical prostatectomy surgery[16]. While this study is unique in that the population considered had prostate cancer, the many additional studies of lycopene consumption addressing cardiovascular, ocular or other clinical endpoints have not been complicated by any adverse effects[24-31]. Together these studies represent treatment of hundreds of subjects without ill effect.

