### **9.3 Molecular**

**Primary – not applicable.**

**Secondary – not applicable.**

### **9.4 Clinical**

We define disease progression as: PSA doubling time within 3 months; any adverse pathological findings at baseline, three, six, nine, or 12 months if extended pattern biopsies are performed with a Gleason sum  $\geq 7$  (see exception below); involvement of  $> 50\%$  of any core;  $> 1/3$  of cores positive; or other incidental evidence of clinical progression (i.e. positive bone scans or lymph node biopsies). Any patient exhibiting progression at any time will be withdrawn from the study and offered standard treatment options. Any patient may also withdraw from the protocol at any time for any reason and be offered standard treatment.

If extended pattern biopsies are performed with a Gleason sum  $\geq 7$ , but with a pattern 4 seen as a microfocus ( $< 2\text{mm}$  in length), this will not exclude the patient from continuing on trial.

Regarding the 4 core research biopsies, if involvement of  $> 50\%$  of any core or  $> 1/3$  of cores are positive, this will NOT exclude the participant from continuing in the study unless a Gleason pattern 4 is seen (if Gleason pattern 4 is seen as a microfocus [ $< 2\text{mm}$  in length] this will not exclude the patient from continuing on trial).

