For the secondary specific aims (aims 1.2 through 1.4 defined above), we will consider a microarray dataset with measurements for 30,000 genes. For this exploratory investigation genes will be treated as being independent so as to first identify all possible genes that may indicate an effect due to the nutritional supplement (Aim 1.2) or to other dietary components (each considered as a binomial variable) (Aim 1.3). Fisher's exact test will be used to determine which genes result in differences in proportions with up or down regulated genes between groups. No adjustment for multiple comparisons will be made. Also, after all patients have had the potential to be followed for at least one year, they will be classified as to whether they had experienced disease progression within 1 year from protocol entry. The same exploratory techniques described above first using the baseline gene expression profile will be carried out to identify genes that may be associated with disease progression (Aim 1.4). Even though any nutritional supplement will be stopped at 3 months from the start of protocol therapy and the duration of any effect is unknown, this analysis will be repeated using the 3-month gene expression profile to identify the effects of any gene that might have been modified by protocol treatment. To account for genes with highly variable expression regardless of study arm, genes whose expression levels change two-fold in more than 20% of men on placebo (comparing three-month to baseline) will

be excluded from subsequent consideration. This might exclude possible predictors of outcome, but if there is variability within the placebo group then the results may be biased. This refining process will isolate potential predictors of nutritional change when assessing the primary as well as the secondary outcomes. Standard microarray gene expression software algorithms will facilitate analyses to determine if there are individual genes or clusters of genes associated with either supplement, dietary component or disease progression[62, 63] . Fisher's exact test will be used to determine which genes result in statistically significant differences between the groups.

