To evaluate the primary study aim, 29 patients will be randomized to the lycopene intervention, 29 to the fish oil intervention and 29 to the control arm. Analysis of 87 evaluable patients is sufficient to detect a 40% difference in the proportion of patients with a 2-fold decrease in *IGF-1* mRNA levels with lycopene or in the *Cox-2* gene with fish oil when compared with the control. The total accrual of 97 patients takes into consideration a 10% dropout rate by the time of the three-month biopsy. The level of significance for a directional test is set at .025 because the control group will be compared with each of the two intervention groups. The power of each test is set at 81% (nQuery).

Descriptive statistics (mean, confidence intervals, median, proportions) will be calculated to characterize the patients' baseline disease features (e.g. age, Gleason score, PSA) and self-reported nutritional dietary data within each arm. Differences between each of the intervention arms and the placebo arm will be assessed using a chi-square statistic for categorical variables, a t-statistic for continuous variables and the Mann-Whitney statistic for distributions. Estimates of the probability of remaining free of disease progression will be calculated using the Kaplan-Meier product limit method. The log rank test will be used to compare tumor progression between each supplement group and the control (Aim 1.5).

The randomized clinical trial design of this study limits the potential for confounding due to other factors, however this will be investigated by comparing the distribution of clinical parameters and other diet/lifestyle factors as well as changes after 3 months of study treatment among the three arms. Unequally distributed factors would only bias the results if they also

correlate with changes in gene expression. If necessary, the Mantel-Haenszel test for a stratified analysis would be performed in evaluating the primary study aim.

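### The 12-month biopsy depends on PSA kinetics, yet progression is recorded as yes or no with no category for unbiopsied men, and the stated biopsy trigger contradicts section 9.4

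*Protocol*

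**What the plan says.** **The biopsy trigger.** Footnote c to the study table (Protocol section 8.6) states that "need for the 12 month TRUS biopsy will be determined by the PSA progression criteria in section 9.4". It then adds that "those whose PSA doubling time remains > 12 months at the final study visit will not be asked to undergo the 12 month biopsy".

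**The endpoint.** Section 9.4 opens with "We define disease progression as: PSA doubling time within 3 months". It goes on to "any adverse pathological findings at baseline, three, six, nine, or 12 months if extended pattern biopsies are performed with a Gleason sum" of 7 or more, together with core-extent criteria and incidental clinical evidence. Men who progress are withdrawn. For the four-core research biopsies, section 9.4 says of the core-extent findings that "this will NOT exclude the participant from continuing in the study unless a Gleason pattern 4 is seen", with an exception for a microfocus.

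**The analyses.** For the gene-progression analysis (Aim 1.4), section 13 says of all patients that "they will be classified as to whether they had experienced disease progression within 1 year from protocol entry". For Aim 1.5 it plans Kaplan-Meier estimates and a log-rank test of each supplement against control. Section 3.2.2.4 and the Interim Analysis part of section 13 close accrual if more than 5 of 10 men on either supplement arm progress by 12 months. None of these places has a category for men without a 12-month biopsy.

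**PSA and the supplements.** Section 2.3 cites a small lycopene study that "showed a decrease in PSA, decrease in tumor volume and decrease in IGF-1 levels", and a tomato-sauce diet study in which PSA also fell. Supplements stop at about 3 months, and section 13 says the duration of any effect is unknown.

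**The concern.** Part of the progression endpoint is seen only if a biopsy is taken, and at 12 months that decision depends on PSA. A man with slow PSA kinetics whose tumour has become adverse on pathology by month 12 will usually not be recorded as progressed. Three uses of the endpoint are exposed:

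- **Aim 1.4.** A gene related to PSA kinetics but not to tumour progression can appear to be linked to progression. This needs no supplement effect.
- **The closing rule.** Unverified progression lowers the count in every arm. Section 10.2 relies on this rule when it says that no patient should be harmed.
- **Aim 1.5.** If a supplement changes PSA doubling time around month 12, the arms are biopsied at different rates and a difference can arise without any effect on the tumour.

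Separately, the trigger in footnote c cannot be applied as written, so who is biopsied is open to local interpretation.

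**Working it through.** **1. The trigger, set side by side.** The only PSA criterion in section 9.4 is a doubling time within 3 months, and a man who meets it has already progressed and is withdrawn. Footnote c refers to that criterion as the trigger, then excuses men whose doubling time remains above 12 months. Under the first half of the footnote, a man with a doubling time between 3 and 12 months does not meet the trigger. Under the second half, he is not excused. The document does not settle his case.

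**2. The plan's own figure.** The Interim Analysis gives a 95% lower bound of 30.4% when 6 of 10 men progress. The exact one-sided 95% bound is the 5% quantile of Beta(6, 5), which is 30.35%. It reproduces. It presumes that progression is fully observed.

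**3. Model for an illustration.** Let *h* be the true 12-month histologic progression rate, *v* the share biopsied at 12 months, and *a* the share who progress by other routes. If being biopsied is independent of true histology, then

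recorded rate = *a* + (1 − *a*) × *h* × *v*.

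The protocol gives a progression rate of about 25%, used here for *h*. It gives neither *v* nor *a*, so both are assumed. The independence assumption has some support in section 2.5: in the cited series of 98 men, PSA measures including velocity did not differ between men with and without progression on re-biopsy.

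**4. Arm comparison, no true effect, *h* = 25%.**

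| Biopsied, placebo vs lycopene | Recorded, *a* = 0 | Ratio | Recorded, *a* = 10% | Ratio |
|---|---|---|---|---|
| 50% vs 50% | 12.5% vs 12.5% | 1.00 | 21.3% vs 21.3% | 1.00 |
| 50% vs 40% | 12.5% vs 10.0% | 0.80 | 21.3% vs 19.0% | 0.89 |
| 50% vs 30% | 12.5% vs 7.5% | 0.60 | 21.3% vs 16.8% | 0.79 |
| 50% vs 20% | 12.5% vs 5.0% | 0.40 | 21.3% vs 14.5% | 0.68 |
| 30% vs 50% | 7.5% vs 12.5% | 1.67 | 16.8% vs 21.3% | 1.27 |

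Take about 32 men per arm (97 / 3), *a* = 0, and a one-sided Fisher test at 0.025 as a stand-in for the log-rank test. The false-positive rate in favour of lycopene is 1.4% if all men are biopsied, 2.9% at 50% vs 30%, and 5.6% at 50% vs 20%.

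**5. Gene association, gene unrelated to true progression, *h* = 25%, *a* = 0.** If 60% of high expressors and 30% of low expressors are biopsied, recorded rates are 15% and 7.5%. The odds ratio is (0.15/0.85) / (0.075/0.925) = 2.2. At 70% vs 20% biopsied, the rates are 17.5% and 5% and the odds ratio is 4.0. With *a* = 10%, these fall to (0.235/0.765) / (0.1675/0.8325) = 1.5 and (0.2575/0.7425) / (0.145/0.855) = 2.0.

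**6. Closing rule, P(6 or more of 10) in one arm, *a* = 0.**

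| True rate | All biopsied | Half biopsied |
|---|---|---|
| 25% | 2.0% | 0.05% |
| 50% | 37.7% | 2.0% |
| 60% | 63.3% | 4.7% |

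With *h* = 50% and *a* = 10%, half biopsied gives a recorded rate of 0.10 + 0.90 × 0.50 × 0.50 = 32.5% and a closing probability of about 7%. If histology were removed from the count, the rate would be 10% and the probability about 0.015%.

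**The case against.** Several points on the other side stand.

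- **There is histology that does not depend on PSA.** Every man is due a 3-month biopsy whose cores go to standard pathology (section 8.3), and section 9.4 removes a man for pattern 4 beyond a microfocus. A reader might infer that a man with slow PSA can never be a histologic progressor. The documents do not support that. However, this biopsy has four cores, comes nine months before the 12-month assessment, and its core-extent findings alone do not take a man off study.
- **No sentence classes unbiopsied men as progression-free.** That is an inference from the yes/no wording, and a statistical analysis plan might handle it. The log-rank test does allow censoring. But censoring a man at his 12-month visit still counts him as event-free until then, and censoring him earlier because of his PSA would be informative.
- **A false benefit for lycopene is not shown.** A reader might infer that lycopene lowers PSA and so would be looked at less often. The cited studies are small and short, supplements stop at 3 months, and the trigger is a doubling time rather than a level. A rebound after stopping would shorten doubling time and lead to more biopsies on lycopene. No PSA effect is cited for fish oil.
- **The biopsy shares are assumed, and the stakes are limited.** Section 3.2.2.3 calls the study underpowered for progression and the gene analysis exploratory. That does not cover the closing rule, which acts on the trial.

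**Conclusion.** The point holds as a weakness in how 12-month progression is ascertained and as a contradiction in the text. It is not a demonstrated bias of known size or direction.

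The contradiction between footnote c and section 9.4 needs no assumption. The loss of histologic events from the interim count requires only that some men with true histologic progression are not biopsied. The distortion of gene associations requires, in addition, a gene related to PSA kinetics. Bias between arms requires that a supplement still affects PSA doubling time when the biopsy is decided. It could then go either way: the illustrative ratios run from 0.40 to 1.67 with no other route to progression, and from 0.68 to 1.27 with 10% progressing by other routes. The true size cannot be computed, because the share biopsied is not given.

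The matter should be put right, but it concerns secondary analyses and the closing rule. The primary mRNA endpoint is untouched.

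**What to change.** 1. Reconcile footnote c with section 9.4 so that one stated trigger applies and doubling times of 3 to 12 months are covered. Which trigger is a clinical decision for the investigators.
2. For Aims 1.4 and 1.5, state that men without a 12-month extended biopsy have unknown, not negative, 12-month histologic status.
3. Report the number biopsied per arm at 12 months and at the interim look, with histologic progression among biopsied men. Say that these men were selected by PSA.
4. Add a sensitivity analysis that uses only findings obtained in every man on the same schedule: 3-month pathology, PSA and clinical criteria.
5. Keep histologic events in the interim harm count. Moving that count, or the main log-rank test, onto PSA and clinical criteria alone would tie the endpoint more closely to PSA and, as shown above, nearly disable the closing rule.

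The cost is wording and analysis only, with no added biopsies. The downside is fewer classifiable men in analyses that are already exploratory. Coding status as unknown makes the selection visible but does not remove it.
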